**Rationale for Composite Outcome:**
This composite endpoint captures both clinical (BMI, hospitalization) and patient-centered (symptom deterioration) measures, aligning with the study’s aim to evaluate the efficacy of psilocybin in reducing the risk of relapse during a critical recovery period.

- Time to **Response:**

A clinically significant improvement in weight and psychological symptoms during the treatment period.

**Criteria**: **BMI Increase**: ≥10% increase in BMI from baseline (e.g., BMI 16 → BMI 17.6) or reaching a BMI ≥18.5 if achievable within the study period.

- Time to **Remission:**

The achievement and maintenance of weight restoration and psychological well-being, with no significant symptoms of anorexia nervosa.

**Criteria**: **Weight Restoration**: BMI ≥18.5 sustained for at least four weeks, or a weight within 90-95% of ideal body weight adjusted for age and height.

- Changes in AN symptom severity (measured by the Eating Disorder Examination from baseline to primary endpoint and follow-up 6 and 12 months.

- Changes in well-being from baseline to primary endpoint and follow-up 6 and 12 month.

- Changes in personality traits from baseline to primary endpoint and follow-up 6 and 12 months

- Changes in brain resting state connectivity (measured by fMRI), and commonly used task-based fMRI paradigms from baseline to primary endpoint. The task-based paradigms will involve food-related conditions, commonly used in the population (Celeghin et al., 2023; Bronleigh et al., 2022) as well as established paradigms involved in processing reward anticipation (Knutson et al., 2000; Ventorp et al 2022)

- Changes in peripheral BDNF measured in platelet-poor EDTA plasma from baseline to primary endpoint.

5. Trial Design and Procedures

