Currently, there are no approved pharmacological treatments for anorexia nervosa (Rahkonen et al., 2022). However, three pilot clinical trials have been approved and activated. NCT04052568 from John Hopkins is currently active. NCT04505189 from Imperial College is finished but not published. The third pilot study assessed the clinical tolerance and safety of 25mg psilocybin supported by psychological intervention in female AN patients with a BMI of 19 (Peck et al., 2023). The study found no significant changes in ECG, vital signs, or suicidality, and all adverse events (AEs) were mild and temporary. Two participants developed asymptomatic hypoglycemia post-treatment, which resolved within 24 hours with no other significant changes in laboratory values. Most participants reported subjectively meaningful experience, and a majority expressed that a second dose would have been beneficial. The study also observed significant reductions in eating disorder symptoms one-month post-treatment.

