4.2 Secondary Objectives

- To evaluate the efficacy of psilocybin with psychological support in reducing AN symptom compared to TAU and time to relapse within 12-month follow-up.

- To investigate potential mechanisms of action through neuroimaging (fMRI), using both resting-state and task-based paradigms for estimation, and biomarker analysis (BDNF levels) with in six-month follow-up.

- To assess changes in mental health, well-being, and personality traits within 12-month follow-up.

- To conduct a qualitative analysis of the subjective experiences of patients, their relatives, and therapists at last follow-up at 12 months.

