4.4 Secondary Endpoints

- Time to **Relapse:**

Defined as a composite outcome during the follow-up period, consisting of:

1. **≥7 % decrease in BMI** compared to post-hospitalization baseline BMI.

Rationale for 7 %: A 7% decrease in BMI reflects a significant deviation from expected weight gain in patients starting at a minimum BMI of 16, signaling potential relapse.

1. **Re-hospitalization for anorexia nervosa-related complications** (e.g., significant weight loss, medical instability). Data of hospitalization will be collected from hospital journal registers.
2. **Initiation of additional intensive psychiatric or nutritional interventions**, including day-patient or inpatient programs. Data of additional interventions will be collected from hospital journal registers.
3. **Self-reported significant deterioration in eating disorder symptoms** (e.g., severe food restriction, purging) as assessed by validated scales such as the Eating Disorder Examination Questionnaire 6.0 (EDE-Q 6.0).

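### Response and remission are defined by weight and psychological improvement but scored on weight alone, so on these two endpoints a participant with unchanged symptoms can count as remitted

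*Protocol*

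**What the plan says.** Protocol section 4.4 gives each of the two endpoints a describing sentence and then a criterion.

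- **Response, description:** "A clinically significant improvement in weight and psychological symptoms during the treatment period".
- **Response, criterion:** "≥10% increase in BMI from baseline (e.g., BMI 16 → BMI 17.6) or reaching a BMI ≥18.5 if achievable within the study period".
- **Remission, description:** "The achievement and maintenance of weight restoration and psychological well-being, with no significant symptoms of anorexia nervosa".
- **Remission, criterion:** "BMI ≥18.5 sustained for at least four weeks, or a weight within 90-95% of ideal body weight adjusted for age and height".

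The same section lists a separate symptom endpoint: "Changes in AN symptom severity (measured by the Eating Disorder Examination from baseline to primary endpoint and follow-up 6 and 12 months". Section 8.1 names EDE-Q 6.0 as the instrument for symptom change. The relapse composite in section 4.4 has a limb for self-reported symptom deterioration on scales such as the EDE-Q. Section 8.1 describes how the relapse components and EDE-Q change are measured but adds no symptom rule for response or remission. Section 10.2 names remission and response rates as binary outcomes for logistic regression.

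**The concern.** Each description joins weight to a psychological condition, and each criterion leaves the psychological condition out. The protocol has not left the point open for later detail: it fixes the criteria, and they conflict with the sentence directly above them. A programmer following the criteria would report as remitted some participants who, by the description, are not.

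The efficacy objective in section 4.2 is "To evaluate the efficacy of psilocybin with psychological support in reducing AN symptom compared to TAU", and the background reports of the psilocybin pilot in anorexia nervosa that "The study also observed significant reductions in eating disorder symptoms one-month post-treatment". Response and remission carry strong clinical names, yet as scored they do not touch the symptom domain. Sections 5.1 and 7.4 also make the offer of psilocybin to control participants depend partly on preliminary efficacy. The protocol does not say which endpoints inform that decision, but a remission rate that means only weight could be read into it.

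**Working it through.** **1. Description against criterion.**

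| Endpoint | Description requires | Criterion requires |
|---|---|---|
| Response | weight and psychological symptoms improve | BMI +10%, or BMI 18.5 |
| Remission | weight restored, psychological well-being, no significant symptoms | BMI 18.5 for four weeks, or 90-95% of ideal weight |

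No EDE-Q or other psychological threshold appears in the right-hand column, and sections 8.1 and 10.2 do not supply one.

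**2. The plan's own figure.** The worked example reproduces: 16 × 1.10 = 17.6.

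**3. Gain needed for response.** The limbs are alternatives, so the needed gain from baseline BMI b is min(1.10 × b, 18.5)/b − 1, or zero if b is already 18.5 or more. The limbs cross at 18.5/1.10 = 16.82.

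| Baseline BMI | Gain needed |
|---|---|
| 16 | 17.6/16 − 1 = 10.0% |
| 17 | 18.5/17 − 1 = 8.8% |
| 17.5 | 18.5/17.5 − 1 = 5.7% |
| 18 | 18.5/18 − 1 = 2.8% |
| 18.5 or more | 0% |

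**4. Who can enter at 18.5 or more.** Section 6.1 sets only a lower limit (BMI above 16) and admits anorexia nervosa in partial remission. Section 6.2 excludes BMI above 21.0 only if held for at least six consecutive months in the 12 months before screening. Entry at BMI 18.5 to 21 is therefore allowed. Such a participant is at the response threshold on day one and meets the remission criterion after four weeks of stable weight, with no change in symptoms. If reaching BMI 18.5 was meant as crossing it from below, the protocol does not say so.

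**5. Timing of response.** The description refers to the treatment period, which the protocol does not define. Section 5.2 places dosing in weeks 1 and 4 and the last integration session in week 5. The criterion refers to the study period, and section 5.2 has participation run to week 52.

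**6. Illustration of the mislabelling; all rates are assumed.** Let w be the share of an arm meeting the weight criterion and q the share of those who also meet a symptom condition. The plan reports w, the description means w × q, and the mislabelled share is w × (1 − q).

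| w, both arms | q, psilocybin / TAU | Reported | As described |
|---|---|---|---|
| 40% | 60% / 30% | 40% vs 40% | 24% vs 12% |
| 30% | 60% / 20% | 30% vs 30% | 18% vs 6% |
| 30% | 80% / 20% | 30% vs 30% | 24% vs 6% |

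In the first row the mislabelled shares are 40 − 24 = 16 and 40 − 12 = 28 percentage points. If w and q are both equal across arms, no difference between arms is hidden and only the label is wrong.

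**The case against.** The strongest reply is that the trial is unblinded, and the protocol's section on study design justification favours relatively objective outcomes such as BMI change. A weight-only endpoint is defensible on that ground, and adding a self-report limb would bring expectancy bias into endpoints that now lack it. This stands as an argument for keeping weight alone. It does not support calling the result remission without significant symptoms.

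Three stronger readings are tempting, and the documents do not support them.

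- A reader might infer that a symptom effect cannot show in this trial. It can: symptom change and well-being are separate secondary endpoints, and symptom deterioration counts towards relapse.
- A reader might infer that these endpoints mainly measure refeeding under usual care. The protocol describes usual care as specialised eating-disorder care, with psychotherapy and temporary day care allowed as part of it. It does not mention refeeding or say what drives weight gain.
- A reader might infer that response demands an implausibly fast gain within the dosing weeks. The treatment period has no stated length, the criterion points to the study period, and the full 10% is needed only at baseline BMI up to about 16.8.

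It is also fair to say that the illustration shows possible mislabelling and not a detectable effect lost. With 20 per arm, 24% vs 12% is about 5 vs 2 participants (Fisher's exact p = 0.41), and the protocol itself says that power for differences between groups is limited.

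**Conclusion.** The inconsistency is real and nothing elsewhere in the protocol repairs it. As written, response and remission are weight endpoints under names and descriptions that promise more. A participant with unchanged eating-disorder symptoms can be counted under either, and one who enters at BMI 18.5 or above could be counted without gaining weight. Response also has two different observation periods.

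The conclusion rests on the text of sections 4.4, 6.1 and 6.2 and not on the assumed rates. The number affected cannot be computed, because the documents give neither the expected baseline BMI distribution nor the overlap between weight and symptom improvement. The reach is limited to these two secondary endpoints in a 40-person pilot whose primary endpoint is safety. The primary conclusion and the EDE-Q change analysis are untouched. It should be corrected because it decides whether the trial may speak of remission at all.

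**What to change.** Reconcile description and criterion in section 4.4 before any summary by arm is seen; in an open-label trial a later choice could be driven by the data. There are two ways:

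1. **Rename.** Call the endpoints weight response and weight restoration, delete the psychological wording, and rest no remission claim on them. This costs only wording and keeps the endpoints objective.
2. **Add the symptom part.** Keep the names and require an EDE-Q condition as well, with a threshold set by the sponsor. Assess it at visits where section 5.2 already lists both BMI and EDE-Q: baseline, week 9 and months 3, 4, 5, 6, 9 and 12. No new visit is needed, but there will be fewer events and an unblinded self-report component. No EDE-Q is listed between baseline and week 9, so response could not be assessed this way during the dosing weeks. The text should say which EDE-Q visit or visits apply to the four-week remission condition.

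Under either option, state one observation period for response, and say how participants already at BMI 18.5 or above at baseline are counted.

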5.1 Overall Trial Design

- A Phase IIa, open-label, randomized controlled trial with two arms:

1. Active treatment arm; Two dosing sessions with psilocybin 25mg with psychological support alongside TAU.

2. Active comparator control arm; TAU only.

TAU includes specialized care offered in an eating disorder unit in Region Skåne, Sweden. If the active treatment arm is determined to be safe, tolerable, and preliminarily effective during the follow-up assessment, participants in the control group will have the option to switch to the active treatment while maintaining their usual specialized care.

This design minimizes ethical concerns regarding withholding a potentially effective treatment.

Participants will be randomly assigned (1:1) to either the intervention or control group.

Block randomization stratified by age group (16–17 and 18–35 years) will ensure balanced representation.

**Rationale for fixed psilocybin 25mg dosing:**

The selected fixed dose of 25 mg is based on extensive use in prior clinical trials, including COMP005 and COMP006 (phase III), and the COMP007 long-term safety follow-up study. All of these protocols employed a fixed 25 mg dose without weight-adjustment and were approved by regulatory agencies in multiple countries. These trials have consistently demonstrated that 25 mg is safe, well-tolerated, and associated with meaningful therapeutic effects.

This approach is also supported by prior studies involving patients with anorexia nervosa, which used similar inclusion criteria and demonstrated safety and therapeutic benefit of the 25 mg dose (Peck et al., 2023). Furthermore, as noted by MacCallum et al. (2022), a secondary analysis of prior psilocybin trials found no significant difference in psychedelic effects between fixed 25 mg dosing and weight-adjusted doses (e.g., 0.29–0.43 mg/kg), reinforcing the rationale for a standardized dose regardless of body weight.

**Rationale for dosing interval:**

Several clinical trials have consistently demonstrated that administering two doses of psilocybin spaced 2 to 4 weeks apart is both safe and therapeutically appropriate when delivered under professional supervision with structured integration support (Bogenschutz et al., 2022; Carhart-Harris et al., 2021; Davis et al., 2021; Garcia-Romeu et al., 2015; Gukasyan et al., 2022). These dosing intervals are grounded in empirical findings from multiple populations and indications. For instance, Carhart-Harris et al. (2021) administered two 25 mg doses of psilocybin three weeks apart to 59 individuals with depression, reporting no serious adverse events (SAEs) and only transient effects such as headache and nausea. Garcia-Romeu et al. (2015) conducted a feasibility study in 15 smokers, administering 20 mg/70 kg and 30 mg/70 kg doses spaced by approximately two weeks; again, no SAEs were reported, and the design highlighted psychological integration. Davis et al. (2021) employed a two-week interval between doses in 24 patients with depression. Finally, Bogenschutz et al. (2022) studied 93 individuals with alcohol use disorder, spacing two 25 mg doses four weeks apart, with no serious adverse drug reactions noted. Collectively, these studies support the 4 week interval as an evidence-based standard that balances therapeutic efficacy with participant safety.

**Rationale for open label randomized controlled trial (not blinded)**

While blinding increases scientific rigor, the likelihood of functional unblinding is high due to the strong experiential contrast between 25 mg psilocybin and a sub-threshold dose such as 1 mg or placebo. This substantially limits the scientific value of using 1 mg psilocybin as an active control. Notably, published trials using low-dose or placebo comparators have not assessed blinding effectiveness—likely because participants can easily distinguish active treatment. These studies should therefore be considered functionally unblinded.

We do not consider it ethical to simulate a blinded design simply for its perceived rigor, when functional unblinding undermines its validity. According to our experience from other studies, participants receiving 1 mg frequently reported frustration at having to undergo 5–6 hours of intensive procedures without any noticeable effects. This is experienced as “placebo,” may lead to reduced trust in the study.

These concerns are amplified in individuals with anorexia nervosa—a psychologically and medically vulnerable group. Extended placebo procedures (e.g., preparation, fasting, lying still with eye mask and music) may cause unnecessary psychological distress when the experience is perceived as ”empty”. Such reactions can negatively affect motivation, retention, and therapeutic alliance.

**Rationale for concomitant antidepressant treatment**

The primary pharmacodynamic mechanism of psilocybin is mediated through agonism at the 5-HT2A receptor. Consequently, medications with direct 5-HT2A-receptor antagonistic effects may block or substantially attenuate the effects of psilocybin and are therefore excluded from psilocybin administration.

In contrast, commonly prescribed antidepressants such as selective serotonin reuptake inhibitors (SSRIs) and serotonin–norepinephrine reuptake inhibitors (SNRIs) do not exert direct 5-HT2A-receptor antagonism. Mandatory discontinuation of these medications, in the absence of a clear mechanistic or safety-based rationale, may expose participants to unnecessary clinical risk, including symptom deterioration and reduced treatment stability.

Given that the present study targets individuals with anorexia nervosa rather than depressive disorders, antidepressant efficacy per se is not a primary outcome. Requiring discontinuation of antidepressants solely based on practices derived from depression trials would therefore be disproportionate in this context.

Available controlled human data indicate that concomitant treatment with SSRIs does not necessarily attenuate the subjective or physiological effects of psilocybin and may reduce anxiety-related adverse effects (Becker et al., 2025). Furthermore, antidepressant discontinuation is associated with clinically relevant risks, including withdrawal symptoms and symptom destabilization. At the same time, observational data suggest that ongoing or recent SSRI/SNRI use may attenuate certain subjective effects of psilocybin, with some reports indicating that this attenuation could persist for several weeks or even months following discontinuation (Gukasyan et al., 2023). However, the magnitude, consistency, and clinical relevance of this potential reduction remain uncertain.

Allowing continued antidepressant treatment when clinically indicated improves patient safety, reduces avoidable treatment disruption, and increases the representativeness of the study population relative to real-world clinical care. This approach supports proportionality and ethical conduct while maintaining the scientific integrity of the intervention and its mechanistic rationale.

**Impact on Treatment as Usual (TAU)**

In this study, the control group receives Treatment As Usual (TAU), consisting of evidence-based care within specialized eating disorder services. Introducing a “placebo” experience with 1 mg psilocybin—when participants recognize it as inactive—may undermine their engagement with TAU. This could introduce a negative expectancy bias, leading to demoralization or nocebo-like effects that reduce adherence and treatment response. In effect, the placebo condition could contaminate the comparator and bias outcomes against the control group, compromising both scientific validity and ethical responsibility.

**Study Design Justification and Endpoint Suitability**

This trial is designed to assess safety and tolerability in a vulnerable population. Results will guide future trials where efficacy becomes the primary objective. At that stage, a larger sample and more complex control design may be justified.

Our current outcome measures—such as BMI change, re-hospitalization, and BDNF—are relatively objective and well-suited for detecting clinically meaningful effects, even without a placebo comparator.

**Statistical Consideration**

With only 40 participants, statistical power to detect between-group differences is limited regardless of blinding. Thus, the trial is appropriately focused on safety, feasibility, and tolerability. Qualitative and neurobiological measures are included to support interpretation.

**Scientific Precedent and Stepwise Development**

As described in the protocol, this trial aligns with established guidance for early-phase psychedelic research (e.g., Johnson et al., 2008). Open-label designs have been widely accepted in early trials involving vulnerable populations and novel treatments. This stepwise approach provides critical groundwork for future efficacy-focused studies.

**Clarification on Targeted Sample Size for Dosing**

The trial aims to dose at least 20 participants in the psilocybin treatment arm. This number refers to participants who receive at least one 25 mg psilocybin session, not only those who are randomized.

Analysis of safety and tolerability will primarily focus on this dosed cohort.

Recruitment will continue until a minimum of 20 participants in the intervention arm have received at least one dose, unless safety or feasibility concerns require early termination.

**5.2 Procedures and Schedule of Assessment**

All procedures will be conducted at the University Hospital for Psychiatry, [name], except the fMRI assessments which are performed at the The National 7T Facility in Lund. All assessments will be carried out by qualified personnel appointed by the principal investigator, including medical doctors, nurses, and psychologists. The National 7T Facility will appoint qualified personnel for fMRI assessment.

The duration of the entire trial is from the first screening of the first patient to the last follow up of the last patient. For each patient participant, the duration of the trial is from the screening to the last follow up at week 52 (12 month).

Patient rehospitalization and additional interventions data are collected in patient journal registers.

**Pre-Study Activity**

Following ethical approval, a focus group will be conducted with patients with anorexia nervosa in two different groups, one aged 16–18 and one 19–35 years. The purpose is to provide study information, gather feedback on the clarity and ethical aspects of the protocol, and identify ways to improve potential benefit. Input from this focus group will inform study quality, recruitment materials, communication strategies and ethical aspects of psilocybin research experienced by the population. Any amendments based on this will be processed according to CTIS protocol.

